## **A. Introduction**

### *Domestic violence and its psychiatric sequelae*

Domestic violence, also referred to as intimate partner violence which overwhelmingly targets women of marriage and cohabitation, is a serious global public health issue with nearly 30% of women who have experienced physical or sexual abuse by their intimate partners.[1]

In Hong Kong, there were 4.5%-10% of women who experienced a physical violence and approximately 14,000 domestic violence cases reported to police offices each year.[2,3] Depression is the most common psychiatric sequela of domestic violence, with an average prevalence of 47.6% among women victims.[2] Our recent study has shown that 65.2% women survivors of intimate partner violence had mild to severe depression.[4] Abused women also often experienced post-traumatic stress disorder (PTSD), anxiety, substance abuse, and even suicidal thoughts. Although multiple psychological therapies, such as advocacy, cognitive behavioral therapy (CBT), and empowerment are a mainstay of domestic violence victim interventions,[5] a large portion of the victims could not achieve satisfactory response and have low acceptability for psychological interventions; this seems to be particularly apparent in Asian women.[6] Psychological interventions may be limited to patients with mild symptoms with long-term engagement of professionals. The development of non-psychological therapies is therefore highly desired.

### *Invasive and non-invasive acupuncture for depression and other stress trauma-related psychiatric symptoms*

Acupuncture has been widely introduced into local clinics and hospitals of Hong Kong. Numerous studies have shown benefits and efficacy of acupuncture in the treatment of various psychiatric disorders, including depression and anxiety.[7,8] In addition to traditional invasive acupuncture in which needles are inserted into acupoints on the body, a non-invasive acupuncture mode called transcutaneous electrical acupoint stimulation (TEAS) also has been used in the treatment of postoperative anxiety, depression, autism, smoking cessation, and drug dependence.[9,10] Compared to invasive acupuncture, obviously, TEAS is more acceptable to patients and physicians as it is non-invasive, safer, and time-saving, without causing pain and needle phobia (Fig. 1).[9,10] Furthermore, TEAS can be performed by patients themselves at home. These suggest that a combination of invasive acupuncture and TEAS could serve as an effective and more acceptable intervention for the victims.

### *Our studies related to domestic violence and acupuncture*

Over the past decade, we have evaluated the effectiveness of advocacy and Qigong interventions in domestic violence women victims.[2,4] We also have completed a series of epidemiological and methodological studies on women victims of domestic violence in local and international communities,[6,11,12] with over 30 related papers published. On the other hand, we have developed a novel acupuncture stimulation called dense cranial electroacupuncture stimulation (DCEAS) based on neuroanatomical rationales.[13] In this mode, electrical stimulation is delivered on dense acupoints located on the forehead innervated by the trigeminal nerve (Fig. 2A). Our several clinical trials have confirmed benefits and efficacy of DCEAS in patients with depression, obsessive-compulsive disorder (OCD), and neuropsychiatric sequelae of stroke.[14-17] Our two large-scale clinical trials have shown that patients with OCD and PTSD achieved an approximately 20% higher clinical remission rate on TEAS combined with CBT and/or antidepressants than those without TEAS.[9,10] These results provide a solid foundation for further evaluation of the effectiveness of combining TEAS and DCEAS.

### *Our studies on biomarkers associated with stress trauma and depression:*

Our recent study has suggested that activity of leukocyte-containing telomerase, a ribonucleoprotein enzyme that maintains chromosome ends, increased following Qigong intervention in women victims of domestic violence.[4] The overexpression of platelet 5-HT1A receptors was correlated with more severe symptoms in patients with depressive disorder.[18] According to the presence and absence of stress trauma prior to its onset, depression can be classified into reactive and endogenous (melancholic) subtypes; domestic violence caused depression belongs to reactive subtype.[19] NALP3, standing for NACHT, LRR and PYD domains-containing protein 3, is an essential component of the inflammasome that modulates the release of cytokines, such as tumor necrosis factor (TNF), interleukin-4 (IL-4), IL-6, and IL-10. Our preliminary study has shown that leukocyte-containing NALP3 was significantly lower in patients with reactive depression than healthy controls and endogenous subtype and the serum brain-derived neurotrophic factor (BDNF) level was significant negatively correlated with the severity of reactive depression.

Determining relationships between potential biomarkers and the severity of psychiatric symptoms will lead us to better understand the pathogenesis of stress trauma and biochemical mechanisms of acupuncture effects.

## **B. Hypothesis and Aims to be Tested**

We hypothesize that additional therapy with a combination of TEAS and DCEAS produces better outcomes than routine care alone in improving depression and other psychiatric sequelae of domestic violence; the therapeutic effects of acupuncture may be associated with varying modulation of blood biomarkers. To test this hypothesis, an assessor-blinded, randomized controlled trial will be conducted to pursue the following the two aims: (1) to compare the effectiveness of routine care with and without additional TEAS and DCEAS in treating depression, and other psychiatric symptoms of domestic violence women victims; and (2) to determine baseline-to-endpoint changes in levels of blood biomarkers, and their correlations with clinical outcomes.

## **C. Plan of Investigation**

**Outline:** This is an assessor-blinded, randomized controlled trial. A total of 110 women victims of domestic violence aged 18-65 years will be recruited from local community centers and domestic violence shelters (refugee centers). They will be randomly assigned to routine care combined with (n = 55) and without (n = 55) additional acupuncture (TEAS+DCEAS) for 12 weeks. The study flow chart are presented in Fig. 3. Acupuncture therapy will be conducted with 2 DCEAS sessions at clinics and 3 TEAS sessions at home each week. The primary outcome is the Beck Depression Inventory II (BDI-II) for depression. Secondary outcomes include the 17-item Hamilton Depression Rating Scale (HAMD-17) for depression, Perceived Stress Scale (PSS) for stress, PTSD Check List-Civilian Version (PCL-C) for PTSD symptoms, Insomnia Severity Index (ISI) for sleep and 12-Item Short Form Survey (SF-12) for quality of life. Two 10-ml blood samples will be drawn respectively at baseline and at the end of 12-week study for measurement of blood biomarkers, respectively. The SPIRIT diagram of all assessments at enrolment, allocation, and different time points can be found in Fig. 4.

### **(i) Subjects**

**(a) Inclusion criteria:** Subjects will be eligible for this study if they: (1) are Chinese women aged 18-65 years; (2) have experienced domestic violence in the previous two years,

confirmed with the Abuse Assessment Screen (AAS) Screen Questionnaire; and (3) are currently experiencing a major depressive episode according to the criteria defined in the Diagnostic and Statistical Manual of Mental Disorders, fifth edition (DSM-5), with a BDI-II score of at least 14.

**(b) Exclusion criteria:** Subjects will be excluded if they have: (1) serious medical conditions or any life-threatening situation that may limit their participation; (2) a history of brain injury or surgery; (3) pregnancy or lactation; (4) investigational intervention in the previous 6 months; (5) heart pacemaker or other metal or electrical devices implanted in the body; (6) serious suicidal ideation or behaviours; (7) history of alcohol or drug abuse in the past year; (8) history of regular electrical acupoint stimulation in previous 6 months; or (9) severe needle phobia.

**(c) Estimation of sample size:**

The sample size for this trial was estimated based on our preliminary trials [9, 15]. According to previous established HAMD-17 to BDI-II conversion metrics [20], the results indicating an approximately difference of 6.55 in the BDI-II score between two groups. A sample size of 55 in each group will be sufficient with a 95% level of significance ( $\alpha$ ), 80% power ( $1 - \beta$ ), and a conservatively assumed standard deviation of 10.8, and a dropout rate of 20%. Therefore, this trial will include 110 subjects.

Disposable acupuncture needles (0.22 mm in diameter and 25 mm in length) will be inserted at a depth of 10-20 mm perpendicularly or obliquely into acupoints. Manual manipulation will be carried out for all acupoints to evoke needling sensation, followed by electrical stimulation. The output peak current and voltage of the machine (model: ITO ES-360) are 6 V and 48 mA, respectively, with constant wave at frequency of 2 Hz and phase duration of 100  $\mu$ s for 30 min. The stimulation intensity will be adjusted to a level at which patients felt most comfortable. The low frequency could produce broader neuromodulation compared to higher frequency. Each session of treatment will last 30 minutes.

**(d) TEAS regimen:** TEAS will be done for 3 times per week for 12 consecutive weeks by participants at home. A training workshop will be conducted to instruct participants how to use TEAS stimulator. Briefly, TEAS will be delivered on the bilateral Nei-Guan (PC6), which is located on the anterior forearm, between the tendons of the palmaris longus and flexor carpi radialis, at the junction of the distal sixth and proximal five sixths of the line connecting the middle points of the wrist and elbow crease (Fig. 1). This acupoint is specifically beneficial for insomnia, sadness, nervousness, palpitation, chest congestion, nausea and vomiting according to traditional Chinese medicine theory. Neuroimaging has shown that acupuncture stimulation on Nei-Guan can modulate a wide range of cortical and limbic brain region activity.

Constant current electrical impulses will be produced from a TEAS apparatus (SDP-330, Yuwell, Suzhou Medical Appliances Co, Ltd., Suzhou, China). Two electrode pads will be adhered onto the acupoint skin. The stimulation frequency will be set at 50 Hz with a pulse width increasing from 30-100  $\mu$ s, and keeping in 100  $\mu$ s at treatment stage. This frequency is the most comfortable and also has been shown to robustly induce the release of endogenous opiate neuropeptides in the central nervous system. The pulse amplitude will be adjusted to a level at which the perception of 'strong but comfortable' is achieved. Each session of treatment will last 30 minutes.

**(e) Post-trial treatment of subjects of routine care group:** Those who are initially assigned to routine care group will have a choice to receive TEAS and/or DCEAS treatment for 12 weeks after they complete the trial. The post-trial treatment will serve as a compensation for their participation.

**(f) Termination criteria and post-termination management:** To ensure participants' safety, those who cannot tolerate TEAS or DCEAS or are hospitalized due to the aggravation of their condition will be discontinued from the study and given individual clinical treatment.

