**(c) Safety assessment, assurance and ethical consideration:**

For each visit to treatment, a standardized case report form will be used to record patients' AEs, including whether any AE has occurred, occurrence time, duration, type of event, severity, management, and its outcome. Also, whether the adverse events are caused by acupuncture would be assessed. The Common Terminology Criteria for Adverse Events (CTCAE) v5.0 criteria will be used to evaluate the severity of each adverse event [22]. All associated research staffs are trained to recognize and respond to all the adverse events. If an adverse event is regarded as a serious adverse event, it will be reported to project investigators ([name]) and Ethics Committee to review immediately. They will decide whether the patient will be temporarily/permanently interrupted from their current treatment, whether

the patient will withdraw from this clinical trial and whether this trial needs to be adjusted or terminated.

Case Record Form (CRF) will be used to record patients' information, assessment, and treatment. In addition to mobile phone, emergency contact numbers will be provided to participants for them to report emergency and seek advice. Ethical approval will be obtained before the recruitment starts. All participants are required to provide written consent. The proposed study will be registered in [www.clinicaltrials.gov](http://www.clinicaltrials.gov).

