##### **(a) Data analysis**

One biostatistician who is blinded to interventions will be responsible for statistical analysis. Descriptive statistics tables will be used to present basic information on all variables. For continuous variables, the mean and standard deviation (or medians, 25th, and 75th percentiles) will be presented; while for categorical variables, the number of participants in each category and its percentage will be presented separately. The analysis will be carried out on the intention-to-treat (ITT) population. All eligible participants will be included in the analysis. Missing data on the primary outcome will be imputed using the multiple imputation method under the missing at random (MAR) assumption followed by sensitivity analysis.

The primary outcome will be analyzed by a linear mixed-effects model with repeated-measures, with adjustment for the baseline; visit, treatment, and the visit  $\times$  treatment interaction as the fixed effect, and individual subject as the random effect. A significant two-way interaction will be considered to demonstrate whether the treatment group has a greater change in the BDI-II score from baseline to assessing points than the routine care group. The effect of the treatment will be estimated by the difference between treatments, and will be presented together with its associated 95% confidence intervals (CIs). A similar approach will be applied to other continuous outcomes.

For the response rate and remission rate, logistic regression, with adjustment for baseline scores, and Chi-square ( $\chi^2$ ) test will be used. The definition of responder is subjects with  $\geq 50\%$  reduction from the baseline BDI-II score; the definition of remission is subjects with BDI-II score less than 10. Subjects who discontinue treatment prior to having a post-baseline BDI-II score will be considered non-responders/not remission.

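### The termination rule ends study participation as well as trial treatment; its intolerance trigger exists in one arm only, so later BDI-II scores go uncollected and the MAR imputation becomes doubtful

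*Protocol*

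**What the plan says.** Section C(ii)(f), on termination, names two triggers, intolerance and hospitalisation for worsening: "those who cannot tolerate TEAS or DCEAS or are hospitalized due to the aggravation of their condition will be discontinued from the study". In full, women who meet either are "discontinued from the study and given individual clinical treatment". No further outcome assessment is described for them.

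Section C(ii)(e) says routine-care women "will have a choice to receive TEAS and/or DCEAS treatment for 12 weeks after they complete the trial", so none of them is exposed to either procedure during the comparison.

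Section C(iii)(c), on safety, handles serious adverse events differently. The investigators and the ethics committee review each case: "They will decide whether the patient will be temporarily/permanently interrupted from their current treatment". Whether she also withdraws from the trial is listed as a separate question.

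The data analysis section under C(iv) states: "The analysis will be carried out on the intention-to-treat (ITT) population" and "All eligible participants will be included in the analysis". Missing primary-outcome data are to be "imputed using the multiple imputation method under the missing at random (MAR) assumption followed by sensitivity analysis". For response and remission, a woman who stops treatment before any post-baseline BDI-II counts as a failure. The rule says nothing of a woman who stops after her first post-baseline score.

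**The concern.** Stopping a treatment and stopping measurement are different decisions. An intention-to-treat comparison protects against bias because women are followed in their assigned arm whether or not they continue treatment. Here the protocol itself ends follow-up, and one of its two reasons cannot arise in the control arm.

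A woman who cannot tolerate the stimulation may well do worse than the women who continue. If her later scores are never collected, imputation under MAR gives her the course of women in her arm with similar earlier scores, most of whom stayed on acupuncture. If her true course is worse than that, the acupuncture mean looks too good. Hospitalisation for worsening between visits raises the same doubt about MAR, because the event may not show in any recorded BDI-II.

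An SAP can choose how to handle missing values, but it cannot recover scores that the protocol told staff not to collect. The decision therefore belongs in the protocol.

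**Working it through.** **1. The plan's own figure.** Inputs from section C(i)(c): difference 6.55, SD 10.8, power 80%, dropout 20%; the data analysis section gives two-tailed 0.05.

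- Normal approximation: n = 2 × (1.960 + 0.842)² × (10.8/6.55)² = 42.7, so 43 per arm; 43/0.8 = 53.75, so 54.
- t-test: 43.66, so 44 per arm; 44/0.8 = 55.

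The stated 55 per group reproduces. Power is 0.81 (0.80 by t-test) with 44 per arm observed and 0.89 with all 55.

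**2. Who can be removed during the 12 weeks.**

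| Trigger | Acupuncture arm | Routine-care arm |
|---|---|---|
| Intolerance of TEAS/DCEAS | possible | not possible |
| Hospitalised for worsening | possible | possible |

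**3. Simple bias formula.** Let p be the share of the acupuncture arm removed, and d the number of points by which those women are worse than MAR predicts. The overstatement is p × d. Neither input is in the documents, so these are assumed ranges:

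- p = 5%, d = 3: 0.15 points (2% of 6.55)
- p = 10%, d = 5: 0.5 points (8%)
- p = 20%, d = 5: 1.0 points (15%)
- p = 20%, d = 10: 2.0 points (31%)

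**4. Simulation.** Assumptions: 55 per arm; baseline and Weeks 3, 6 and 12; SD 10.8 at each visit; correlation 0.7 between adjacent visits, decaying as 0.7 to the power of the lag; removal after Week 6; intolerance correlated 0.5 with the Week 12 score; missing Week 12 scores predicted within arm from the earlier visits; 3,000 replicates. Entries are the Week 12 difference, routine care minus acupuncture, with complete data → under MAR.

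| Removed | True effect 0 | True effect 6.55 | Shift |
|---|---|---|---|
| 5%, acupuncture only | 0.01 → 0.33 | 6.61 → 6.93 | 0.32, 0.32 |
| 10%, acupuncture only | −0.02 → 0.58 | 6.51 → 7.09 | 0.60, 0.58 |
| 20%, acupuncture only | −0.06 → 0.95 | 6.51 → 7.53 | 1.01, 1.02 |
| Worst 5%, both arms | −0.06 → −0.06 | 6.52 → 6.52 | 0.00, 0.00 |
| Worst 10%, both arms | 0.03 → 0.02 | 6.55 → 6.54 | −0.01, −0.01 |
| Worst 5% both, plus 10% acupuncture | −0.01 → 0.42 | 6.58 → 7.01 | 0.43, 0.43 |

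The one-arm shift is 0.32/6.55 = 5% to 1.01/6.55 = 15% of the planned difference. It is the same when the true effect is zero.

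**5. Effect on the test, roughly.** The unadjusted standard error with 55 per arm is 10.8 × √(2/55) = 2.06. With no true effect, the chance of a significant result favouring acupuncture is nominally 2.5%. A shift of 0.6 moves the threshold from 1.96 to 1.96 − 0.6/2.06 = 1.67, which gives about 4.8%. A shift of 1.0 moves it to 1.47, which gives about 7%.

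**The case against.** Five points can fairly be made on the other side.

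- **Poor outcomes are not deleted.** A reader might infer that bad results vanish from the analysis. They do not: all eligible participants are included, scores taken before discontinuation remain in the mixed model, later ones are imputed, and women with no post-baseline BDI-II count as failures on response and remission. Only the later outcomes are unobserved. This stands.
- **ITT is not literally contradicted.** Keeping each woman in her assigned arm and imputing missing values is a coherent analysis. Nor is MAR shown to fail: hospitalisation after worsening already recorded at Week 3 or 6 is compatible with it. What remains is doubt about the assumption.
- **Hospitalisation need not favour acupuncture.** It applies to both arms and at equal rates leaves the difference essentially unbiased. If acupuncture works, more control women might be hospitalised, which would push the other way. Only the intolerance trigger supports a direction.
- **Larger bias figures are tempting.** Taking the planned 20% dropout as removal under this rule, and multiplying by 6.55 or by one SD, gives 0.20 × 6.55 = 1.31 or 0.20 × 10.8 = 2.16 points. But the 20% is an overall dropout allowance for sample size, and 10.8 ignores the earlier scores on which imputation conditions. These are upper cases.
- **A sensitivity analysis is promised, and its method may be in the SAP.** This is right, and the lack of a named method is not part of this point.

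It can also be said that leaving the study may be loose wording for stopping treatment. But section C(iii)(c) separates the two, so the protocol knows the difference, and C(ii)(f) provides for no assessment afterwards. At the least the sections need reconciling.

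**Conclusion.** The point holds in a limited form. As written, the termination rule makes study exit automatic. One of its triggers is confined to the acupuncture arm, and outcomes after exit are not provided for. This undermines the purpose of ITT and makes MAR doubtful for the women concerned. The rule also sits badly with the case-by-case decisions in the safety section: a hospitalisation reported as a serious adverse event would fall under both. The failure rule for response and remission covers only those who leave before a first post-baseline score.

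The plausible size is about 0.3 to 1.0 BDI-II points in favour of acupuncture. This rests on assumed removal of 5% to 20% of that arm, a 0.5 correlation between intolerance and the Week 12 score, and Week 3 and 6 scores being available. If intolerance is rare or unrelated to outcome, the bias is negligible. The effect is modest against 6.55, but it tends to favour the tested treatment and is cheap to prevent. The clinical criteria for stopping treatment are not questioned.

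**What to change.** Leave the treatment-stopping criteria unchanged and amend three sections so that they agree:

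- **Termination, C(ii)(f), and safety, C(iii)(c):** separate stopping trial treatment from leaving the study, and say how the two rules fit together when a hospitalisation is also a serious adverse event.
- **Follow-up:** state that every randomised woman who has not withdrawn consent continues the scheduled Week 3, 6 and 12 assessments where feasible. The minimum is the BDI-II, obtained by a contact route that is safe and confidential for her. Post should not be the default for victims of domestic violence, and the HAMD-17 needs a clinician.
- **Data analysis, C(iv):** state that scores collected after treatment stops enter the ITT analysis, and extend the response and remission rule to women who stop after a first post-baseline score.

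The cost is a short amendment, a few extra follow-up contacts and possibly a slightly smaller estimated effect. The sample size does not change, and each retained score moves power from about 0.80 (44 per arm observed) towards 0.89 (all 55).
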